### Data analysis plan

2.5

Descriptive statistics will be presented as median (interquartile range) or number (%). For the single group study, we will use the normal approximation method to calculate 95% confidence intervals for proportions, including the primary outcome. Comparisons between baseline and one‐year follow‐up measurements will involve paired analyses, for example, McNemar's test for categorical data and paired t‐test or a non‐parametric equivalent for continuous data, depending on the data distribution. The analyses will be stratified by age groups, sex, and previously established cardiovascular risk factors. All tests will be two‐sided and considered statistically significant at *p* < 0.05.

The cohort study examines time to the different events of interest. We will use the Kaplan–Meier method and Cox proportional hazards regression to evaluate all‐cause mortality. For other events of interest, death will be accounted for as a competing risk. Survival times are calculated from the initial consultation until either the event of interest, death or study end, whichever comes first. To compare baseline group differences, we will utilize the Fisher exact test, the *χ*
^2^ test, or the Mann–Whitney *U* test, depending on the data characteristics. We do not anticipate any significant group differences; however, we will perform univariable and multivariable regression analyses to identify and adjust for any relevant covariates (age, sex, medical history, prescriptions of drugs used for cardiovascular prevention). Subgroup analyses will comprise previously “healthy” individuals (no drug prescriptions related to cardiovascular prevention) and individuals without established cardiovascular disease (defined as not being prescribed antiplatelet agents or anticoagulants). Analyses will also be stratified by age groups and sex.

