### Outcomes

2.4

The purpose of the prospective single group trial is to assess the prevalence of vascular risk factors and the impact of screening on subsequent management and vascular risk. The primary outcome is the proportion of cases receiving pharmacological intervention following the vascular risk factor evaluation; pharmacological intervention is defined as the initiation or dose adjustment of antihypertensive agents, antidiabetic agents (including SGLT2 inhibitors used for other indications), lipid‐lowering agents, antiplatelet agents, or anticoagulants (Table 2). Secondary outcomes are as follows: (i) proportion of cases where the screening procedure uncovers previously undetected vascular risk factors, subdivided into hypertension, diabetes mellitus, moderate‐to‐severe chronic kidney disease, and atrial fibrillation, (ii) alterations in modifiable vascular risk factors at the one‐year follow‐up compared to baseline measurements, (iii) changes in SCORE2/SCORE2‐OP risk scores at the one‐year follow‐up, specifically in individuals without established cardiovascular disease, (iv) proportion of participants with adverse effects following pharmacological intervention, (v) proportion with arrythmias or QT‐prolongation captured during admissions, and (vi) proportion of participants remaining on initiated treatment at the 12‐month follow‐up.

**TABLE 2 epi412987-tbl-0002:** Variables and outcomes for the two analyses.

Variables	Primary outcome	Secondary outcomes
One‐year single group prospective analysis		
See Table 1	% with pharmacological intervention	Hypertension, diabetes mellitus, moderate‐to‐severe chronic kidney disease, atrial fibrillation, alterations in modifiable vascular risk factors compared to baseline, changes in SCORE2/SCORE2‐OP at the one‐year follow‐up, % adverse effects
Matched cohort long‐term analysis		
Demographics, vascular disease, comorbidities that can cause seizures, medical treatments	Stroke	Major adverse cardiovascular events, all‐cause mortality, stroke severity (NIHSS at stroke admission; modified Rankin Scale 3 months post‐stroke), conduction block/arrhythmia, and occurrence of recurrent seizures

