### Sample size calculation

2.6

The incidence of late‐onset seizures is about 60 per 100 000 person‐years.^15^ Among these cases, approximately two‐thirds do not have an identifiable cause, such as a brain tumor. Participating health service regions cover about 5 million inhabitants and should have at least 1000 potential cases yearly. For the primary outcome of the single group analysis (proportion of cases undergoing pharmacological intervention), we aim for a margin of error less than 5%, which would translate to a minimum sample size of 385 (using an estimated proportion of 50%; for lower proportions, the required sample size generally decreases). For the cohort study, a 10‐year stroke risk of 10% and an effect of the intervention of 30% risk reduction translate to a need for 1021 participants post‐intervention and 2045 participants pre‐intervention to detect a difference in 10 years. Participating sites should cover approximately 1000 cases in the right age group per year, allowing inclusion of up to 2000 patients over 2 years and 4000 historic controls over 4 years. The vascular risk is not evenly distributed over time, the risk is greatest in the first years, but we should be able to detect a difference after 5–10 years.

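### Normal-approximation intervals are fixed for every single-group proportion with no low-count exception; if a secondary proportion turns out low, they under-cover and the upper limit is too low

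*Protocol article*

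**What the plan says.** For the single-group trial, the Data analysis plan (2.5) states: "we will use the normal approximation method to calculate 95% confidence intervals for proportions, including the primary outcome". Naming the primary outcome as included implies that the other proportions are covered as well. No alternative is given for small counts, although the same section allows a non-parametric substitute for the paired t-test and lists Fisher's exact test for baseline comparisons in the cohort study.

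The secondary outcomes in Outcomes (2.4) include several proportions: previously undetected risk factors, split into hypertension, diabetes, chronic kidney disease and atrial fibrillation; arrhythmia or QT prolongation captured during admissions; persistence on treatment at 12 months; and the "proportion of participants with adverse effects following pharmacological intervention". The Data analysis plan adds: "The analyses will be stratified by age groups, sex, and previously established cardiovascular risk factors".

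The Sample size calculation (2.6) sizes this part for the primary outcome only, "which would translate to a minimum sample size of 385", on an assumed proportion of 50%.

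**The concern.** The normal-approximation (Wald) interval works well for a proportion near one half with several hundred patients. It works badly when few events are expected. It is centred on the observed proportion, and its width is computed from that same proportion, so a chance shortfall in events both lowers the estimate and narrows the interval. The misses then fall mainly on one side, with the upper limit below the true rate.

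That is the unhelpful direction for adverse effects, where a reader looks to the upper limit to see what has been ruled out. Negative lower limits and zero-width intervals would also look odd in print and invite a change of method after the data are seen.

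**Working it through.** **Inputs from the protocol article.** Two-sided 95% level, z = 1.96; minimum n = 385; planning proportion 50%; target margin below 5 percentage points (Data analysis plan; Sample size calculation).

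**Assumed inputs.** True secondary rates are not given; 0.2% to 10% is examined. Smaller denominators are not given either; 193 stands for treated patients only if half of 385 are treated (0.5 × 385 = 192.5), and 100 for a stratum.

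**Step 1: the plan's own figure.** n = z²p(1−p)/d² = 1.96² × 0.5 × 0.5 / 0.05² = 384.15, rounded up to 385. The margin at 385 is 4.99 points. The stated size is reproduced.

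**Step 2: limits at low counts.** Wald limits are x/n ± 1.96·√[(x/n)(1−x/n)/n]. With n = 385:

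| Events | Wald | Wilson | Clopper-Pearson |
|---|---|---|---|
| 0 | 0% to 0% | 0% to 0.99% | 0% to 0.95% |
| 1 | −0.25% to 0.77% | 0.05% to 1.46% | 0.01% to 1.44% |
| 2 | −0.20% to 1.24% | 0.14% to 1.87% | 0.06% to 1.86% |
| 3 | −0.10% to 1.66% | 0.27% to 2.27% | 0.16% to 2.26% |
| 4 | 0.03% to 2.05% | 0.40% to 2.64% | 0.28% to 2.64% |

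The Wald lower limit is negative for 1, 2 or 3 events. It is exactly 0 for none, where the interval has no width. The probability of 1 to 3 events is 73% at a true rate of 0.5%, 44% at 1%, 5% at 2% and 0.3% at 3%.

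**Step 3: exact coverage at n = 385.** Coverage is the sum of the binomial probabilities of all counts whose interval contains the true rate p. The chance that the upper limit lies below p is summed in the same way.

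| True rate | Wald coverage | Wald upper limit below true rate (nominal 2.5%) | Wilson coverage |
|---|---|---|---|
| 0.2% | 53.7% | – | 95.7% |
| 0.5% | 85.4% | 14.5% | 95.4% |
| 1% | 89.2% | 10.2% | 93.7% |
| 2% | 94.4% | 5.0% | 95.9% |
| 3% | 93.7% | 5.6% | 96.5% |
| 5% | 93.8% | 5.0% | 95.4% |
| 10% | 94.3% | 4.0% | 95.9% |
| 50% | 94.7% | – | 94.7% |

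Two entries can be checked by hand. At 0.5%, only x = 0 gives an upper limit below the true rate: 0.995^385 = 14.5%. At 1%, x = 0 and x = 1 do (upper limits 0% and 0.77%; x = 2 already reaches 1.24%): 0.99^385 + 385 × 0.01 × 0.99^384 = 2.1% + 8.1% = 10.2%.

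Wilson upper limits fall below the true rate 0% to 2.1% of the time over 0.5% to 10%. Clopper-Pearson coverage is at least 95.9% at every rate in the table.

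**Step 4: other denominators (Wald coverage).**

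| True rate | n = 100 (assumed) | n = 193 (assumed) | n = 2000 |
|---|---|---|---|
| 1% | 63.3% | 85.5% | 94.9% |
| 2% | 86.6% | 89.4% | 94.5% |
| 3% | 80.2% | 92.5% | 94.8% |
| 5% | 87.7% | 91.5% | 94.7% |

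The 2000 is the ceiling in the Sample size calculation ("allowing inclusion of up to 2000 patients over 2 years"). It is a figure for the cohort study and is used here only as an upper bound on trial enrolment.

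**Step 5: the primary outcome.** For 192 of 385, Wald gives 44.9% to 54.9% and Wilson 44.9% to 54.8%.

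**The case against.** The strongest reply is that nothing in the document shows these proportions to be rare. A reader might infer that newly found atrial fibrillation and adverse effects are rare events whose intervals will certainly be badly wrong. The document does not support that. It gives no rate for either, and its ethics section describes side effects as generally mild, which says nothing about how often they occur. Adverse effects of any severity across five drug classes may be common, and undetected hypertension or persistence on treatment need not be low. At 385 patients and true rates of 2% or more, overall coverage is close to nominal and negative limits are unlikely. This stands, and it makes the point conditional.

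It is also fair that 385 is a minimum, that the denominators of 193 and 100 are assumed, and that the plan does not say every secondary proportion will get an interval in every stratum. No test, threshold or stopping rule hangs on these descriptive intervals. With 2 events in 385 the Wald and Wilson upper limits differ by only 1.87 − 1.24 = 0.63 percentage points. All of this limits the weight of the point.

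Two things do not stand. Small-count handling is often left to an analysis plan, but here the protocol names a method for proportions and allows no exception, so this is a stated choice and not an omission. And near-nominal overall coverage at 2 to 10% hides an imbalance: the upper limit is too low at roughly twice the nominal frequency.

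**Conclusion.** The point holds as a minor, conditional one. The plan fixes Wald intervals for all single-group proportions. At the minimum of 385:

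- if a true rate is between about 0.5% and 1%, coverage is about 85 to 89%, and it is lower still below that;
- if it is between 2% and 10%, coverage is about 94%, with the upper limit below the true rate 4 to 6% of the time against a nominal 2.5%;
- with 1 to 3 events the lower limit is negative, and with none the interval collapses to a point.

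In the assumed smaller denominators, coverage at rates of 2 to 5% is 80.2% to 92.5%. With enrolment far above 385 the problem largely goes away (94.9% at n = 2000 and a 1% rate). Which of these applies depends on secondary rates and denominators that the document does not give. The primary outcome near 50% and the sample size are not in question.

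**What to change.** In the Data analysis plan, replace the normal approximation with the Wilson score interval for all proportions in the single-group trial, or with Clopper-Pearson if coverage of at least 95% is wanted. Neither gives a negative limit, and both give a usable upper limit when no events are seen (0.99% and 0.95% for 0 of 385).

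The cost is one phrase. The sample size of 385, data collection and conduct are unchanged, and the primary interval moves by about 0.1 percentage point at most under Wilson.

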### Rationale

1.2

Since there can be a long latency between a first seizure and stroke, and since benefits of treatment of many vascular risk factors are well established, a standard RCT is logistically and ethically challenging. Swedish comprehensive health registers allow a multicenter register‐based randomized controlled trial (RRCT) design, but even with the advantages of that approach recruitment would be challenging. A 1:1 randomized study that assumes a 10‐year cumulative stroke rate of 10% and a 30% relative risk reduction from the intervention would require 247 events and 4494 participants to be completed in 5 years (*α* = 0.05; *β* = 0.2; censoring rate = 0.1). Since all potentially recruitable cases in Sweden are roughly 2000 candidates per year (incidence of late‐onset seizures: ~60 per 100 000), this is not a feasible study design. Furthermore, the benefits of treatment of hypertension and diabetes as well as smoking cessation are well known, making it ethically dubious to withhold such interventions from a control group. Since the research question is not whether vascular risk factor assessment is beneficial, but whether vascular risk assessment specifically in the work‐up of late‐onset seizures is beneficial on a system level, we decided on a cluster‐based design.

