### Intervention: Evaluating modifiable vascular risk factors

2.2

The evaluation of vascular risk factors aims to identify and manage modifiable vascular risk factors early, in line with the current ESC guidelines on cardiovascular disease prevention.^12^ Like most work‐up protocols, investigators may refrain from evaluating selected cases when such intervention is deemed inappropriate or the benefit of potential cardiovascular prevention is minimal. To promote adherence to the practice change, relevant health care staff will receive information during a 6‐month “briefing and implementation phase,” during which they can also report barriers to adherence and suggest site‐specific logistical improvements.

The examinations included in the work‐up are at the investigator's discretion to align with existing local guidelines; however, the minimum requirements are listed in Table 1. A registered nurse or a nursing associate will generally be available with each initial consultation to conduct any ordered examinations, minimizing the need for additional visits. Using composite risk assessment tools, for example, SCORE2/SCORE2‐OP, is advised to guide preventive measures in individuals without already established cardiovascular disease. Investigators are free to give lifestyle advice and prescribe medications according to local or international guidelines and to tailor treatment according to the patient's preferences; the study protocol does not specify any management strategies for identified conditions beyond what existing Swedish guidelines already recommend. Participating sites will have regular education on what the guidelines stipulate regarding blood pressure targets, lipid level targets, and smoking cessation.

**TABLE 1 epi412987-tbl-0001:** Mandatory components of the vascular risk factor evaluation.

Procedure
Family history of vascular disease
Tests/examinations (order or obtain from medical records [past 3 months])
Weight
Height
Waist circumference
12‐lead ECG
Resting and standing blood pressure
Total cholesterol
HDL cholesterol
LDL cholesterol
HbA1c
High sensitivity CRP
Serum creatinine
Urine albumin‐to‐creatinine ratio
Medical history
Atherosclerotic cardiovascular disease
Atrial fibrillation
Congestive heart failure
Diabetes mellitus
Hypertension
Kidney disease
Life‐style risk factors (smoking, exercise)

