### Sample selection

2.3

Patients undergoing their first‐ever specialized assessment for unprovoked seizures or epilepsy with onset after age 50, who also receive a vascular risk factor evaluation (minimum requirements are outlined in Table 1) in conjunction with their initial consultation (within 1 month), are invited to participate in a prospective one‐year trial. Individuals unable to provide informed consent and those with established progressive brain disease, that is, brain tumor or neurocognitive disorder, will be excluded. Notably, we will not exclude patients already on primary or secondary cardiovascular prevention; thus, the study will include groups for whom the benefit from the intervention may be limited.

In addition, we will conduct a system‐level register‐based cohort study based on data from the National Patient Register (NPR), which covers information on all specialized health care encounters in Sweden, and the Swedish Prescribed Drug Register (SPDR), which encompasses details of all prescribed drugs dispensed at pharmacies. Patients aged ≥50 with a first‐ever outpatient appointment to one of the participating clinics and a first‐listed diagnostic code for seizures or epilepsy (ICD‐10: R568, G40) are included. Exclusion criteria will be (i) preexisting seizures/epilepsy, as demonstrated by a registered diagnostic code for seizures (ICD‐10: R568, G40, G41) or a dispensed antiseizure medication (ATC‐code: N03) more than 3 months before the initial consultation, (ii) a registered diagnostic code for stroke or TIA (ICD‐10: I61, I63, I64, or G45 except G454) before the initial consultation, or (iii) progressive brain disease, as indicated by diagnostic codes or drug prescriptions suggestive of brain tumors (ICD‐10: C71, D33, D43, C793) or neurocognitive disorders (ICD‐10: F00‐F03, F051, G30, G318, G912; ATC code: N06D). The only difference in eligibility criteria between the intervention group and the control group will be the period of recruitment; the former will consist of patients with their initial consultation in the 2 years following the “briefing and implementation phase” of the center, whereas the control group will encompass those seen in the four preceding years at the same site.

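### Controls are followed well past their own clinic's practice change, so any later screening of controls would pull the stroke comparison towards no effect, and nothing in the plan measures or allows for this.

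*Protocol article*

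**What the plan says.** The cohort study compares two groups from the same clinics. The intervention group has its first visit in the two years after the clinic's briefing phase, "whereas the control group will encompass those seen in the four preceding years at the same site" (Sample selection).

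Follow-up is the same for both groups: "Survival times are calculated from the initial consultation until either the event of interest, death or study end, whichever comes first" (Data analysis plan). Outcomes sets a horizon of at least 5 years, and Sample size calculation expects a detectable difference after 5 to 10 years.

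The new work-up applies at the first specialised consultation (abstract, Study design, Sample selection). The education of staff is not limited in that way: "Participating sites will have regular education on what the guidelines stipulate regarding blood pressure targets, lipid level targets, and smoking cessation" (section 2.2).

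The sample size rests on "a 10‐year stroke risk of 10% and an effect of the intervention of 30% risk reduction", giving "1021 participants post‐intervention and 2045 participants pre‐intervention to detect a difference in 10 years". Expected recruitment is larger, "allowing inclusion of up to 2000 patients over 2 years and 4000 historic controls over 4 years".

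**The concern.** A control first seen one year before the change may come back for seizure follow-up and meet staff who have been briefed on vascular risk and are regularly taught blood pressure, lipid and smoking targets. Nothing in the protocol keeps that patient from being assessed and treated, and the survival-time rule counts the person as a control to study end.

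Spill-over of this kind runs one way. It makes controls look more like the intervention group and moves the stroke estimate towards no effect. A null result could then mean either that screening at the first visit does not help, or that some controls were screened later. The protocol describes no analysis that would tell these apart. The issue concerns what happens to controls after entry, so it remains however the four-year window is dated.

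**Working it through.** **1. The plan's own figure.** The inputs are a 10-year risk of 10% in controls and a 30% reduction (Sample size calculation) and two-sided testing at 0.05 (Data analysis plan). Power of 80% is stated in Rationale only for the rejected randomised design, and I assume that it carries over.

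- Events needed with 1:2 groups: (1.96 + 0.84)² / [(2/9) × (ln 0.70)²] = 278.
- Ten-year risk under a hazard ratio of 0.70: 1 − 0.9^0.7 = 7.1%. Average risk: (2 × 10% + 7.1%)/3 = 9.04%.
- Total patients: 278/0.0904 ≈ 3076, or about 1025 and 2051.

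A pooled two-proportion formula (7% v 10%) gives 1038 and 2076. Both agree with the stated 1021 and 2045 to within 2%. Neither needs a crossover term, so the stated numbers assume the full contrast.

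**2. Share of control time after the change** (even entry, deaths ignored). Share = 1 − (mean pre-change time)/T.

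| Control entry before the change | Mean pre-change time | T = 5 | T = 10 |
|---|---|---|---|
| 0 to 4 years | 2 years | 60% | 80% |
| 0.5 to 4.5 years (6-month briefing phase left out) | 2.5 years | 50% | 75% |

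**3. Dilution.** The documents give no crossover rate, so I assume that a fraction q of post-change control time is exposed, with full effect at once and a constant hazard. Observed HR = 0.70/(1 − 0.30 × q × share), using shares of 60% and 80%. Power = Φ(√(D × 2/9) × |ln HR| − 1.96), where D is the number of strokes.

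- 1021/2045 over 10 years: D ≈ 278.
- 2000/4000 over 10 years: D = 4000 × 10% + 2000 × 7.1% ≈ 542.
- 2000/4000 over 5 years: D = 4000 × 5.13% + 2000 × 3.62% ≈ 278.

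| q (assumed) | HR, 10 y | Power, 1021/2045, 10 y | Power, 2000/4000, 10 y | HR, 5 y | Power, 2000/4000, 5 y |
|---|---|---|---|---|---|
| 0 | 0.70 | 80% | 97% | 0.70 | 80% |
| 10% | 0.72 | 74% | 95% | 0.71 | 76% |
| 30% | 0.75 | 60% | 87% | 0.74 | 66% |
| 50% | 0.80 | 44% | 71% | 0.77 | 54% |

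A second model moves a fraction of controls from the 10% to the 7% ten-year hazard at the change, with entry 0.5 to 4.5 years before it. For fractions of 10, 30 and 50% it gives 10-year risk ratios of 0.72, 0.75 and 0.79. Power is 73, 59 and 43% at 1021/2045, and 96, 87 and 71% at 2000/4000.

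**4. What censoring controls at the change would leave.** With entry over 0 to 4 years, constant hazard, HR 0.70 and intervention patients cut at 4 years, 2000/4000 yields about 83 control and 58 intervention strokes. Log-rank power is about 52%. At 1021/2045 it is about 30%.

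**The case against.** A reader might infer that part of the control group does cross over. The documents do not support that. The work-up belongs to the first consultation, which controls have already had. The protocol does not say that returning patients are screened or how many return. Staff education makes spill-over plausible and no more.

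A reader might also infer that follow-up to study end is an error. It is not. The stated question is a system-level one, and classifying patients by period of first visit is a legitimate policy contrast. The comparator was never unscreened care either, because Objectives and the ethics section both say that opportunistic assessment is already advised in Sweden.

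Three points on size also stand. At 2000/4000 the 10-year power loss is modest for exposure up to 30%. The protocol says that risk is greatest in the first years, so a larger share of control strokes falls before the change than the person-time shares suggest, and the dilution is smaller than tabulated. The censored analysis is weak: its power is below that of every diluted scenario above at the same sample size.

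Finally, sensitivity analyses are often left to an analysis plan that is not shown. That is fair for the details. But the protocol itself fixes the same-site controls, the follow-up rule and a sample size with no allowance for contamination. The figure of 2000/4000 is a ceiling, at 5 years it starts from only 80% power, and more patients do not remove bias.

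**Conclusion.** The point holds as a risk that the plan neither measures nor allows for. Half or more of control person-time at 5 years, and three quarters or more at 10 years, comes after the control's own clinic changed practice. Any later screening of controls biases the stroke effect towards the null.

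The size depends on a crossover rate that the documents do not give. For assumed exposure of 10 to 50%, the 10-year hazard ratio moves from 0.70 to between 0.72 and 0.80. The cost in power is serious at the minimum sample size and at 5 years, and modest at 10 years with the maximum sample unless exposure is high. Constant hazard and an immediate full effect put these figures at the upper end for a given exposure. The main consequence is for how a null stroke result can be read. It does not invalidate the primary analysis.

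**What to change.** 1. Keep the full-follow-up analysis as primary. Describe it as a contrast by consultation period: screening at the first visit against usual care with possible later screening.
2. From the Swedish Prescribed Drug Register, already a source for the cohort, report new starts of cardiovascular-prevention drugs in controls before and after their clinic's change date, by time since consultation. This measures contamination directly.
3. Add a supporting analysis of stroke that censors each control at the start of its clinic's briefing phase and limits intervention patients to the same maximum follow-up of 4 years. Read it as an estimate with its confidence interval, not as a test.

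The cost is plan wording, one table and one extra analysis from data already to be extracted, plus each clinic's briefing date. The drawback is that the supporting analysis has low power (about 52% at 2000/4000 and 30% at 1021/2045) and cannot address the 5-10 year aim.

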## Abstract

**Objective:**

A growing body of evidence suggests patients with late‐onset seizures are at an increased risk of stroke, but the potential for reducing cardiovascular morbidity through risk factor screening and management is unknown. We aim to determine whether individuals with new‐onset unprovoked seizures after middle age should undergo vascular risk assessment. The long follow‐up needed to assess stroke risk and the known benefit of vascular risk factor modification make a standard RCT logistically and ethically challenging. Instead, we propose and have developed a protocol for a cluster project assessing the effect of vascular risk factor screening in an intervention trial as well as a cohort study.

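### The cohort study is built on clinics, but the listed covariates, strata and sample size all treat patients as independent, so clinic-specific before-after changes would make the stroke CI too narrow

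*Protocol article*

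**What the plan says.** The Rationale (1.2) asks whether vascular risk assessment in this work-up "is beneficial on a system level, we decided on a cluster‐based design". Under Study design (2.1) it is the clinics that adopt the new standard of care.

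Sample selection (2.3) defines exposure by clinic and date. The intervention group is "patients with their initial consultation in the 2 years following the “briefing and implementation phase” of the center", while "the control group will encompass those seen in the four preceding years at the same site". Every clinic therefore supplies patients to both periods.

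The Intervention section (2.2) leaves room for clinics to differ: "The examinations included in the work‐up are at the investigator's discretion to align with existing local guidelines", subject to the minimum set in Table 1. Prescribing and lifestyle advice follow guidelines and patient preference.

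The Data analysis plan (2.5) gives the cohort covariates as "age, sex, medical history, prescriptions of drugs used for cardiovascular prevention" and adds: "Analyses will also be stratified by age groups and sex". For stroke it says that death is a competing risk but names no regression model; Cox regression is named for all-cause mortality. No clinic term, random effect or clustered variance is mentioned.

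Sample size calculation (2.6) requires 1021 post-intervention and 2045 pre-intervention patients and expects up to 2000 and 4000.

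**The concern.** When exposure is set by clinic and calendar period, the before-after contrast is in effect estimated once per clinic and then averaged. If the true change in stroke rate varies between clinics, because of local trends in stroke prevention or case mix or because of uneven uptake of the work-up, that variation adds to the uncertainty of the average. It shrinks with the number of clinics, not with the number of patients. A patient-level analysis counts only the patient-level part.

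At stake is the primary outcome of the cohort study, in a comparison with historical controls. An interval that is too narrow could make a modest before-after difference look firmer than it is. The problem also grows with follow-up: the patient-level variance falls as strokes accumulate, and the clinic-level part stays where it is.

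**Working it through.** **1. Reproduce the plan's sample size.** Inputs from 2.6: 10-year stroke risk 10%, 30% reduction, 1:2 allocation. Two-sided 5% comes from 2.5. Power of 80% is stated in 1.2 only for the rejected randomized design and is assumed to carry over.

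- Schoenfeld: events = (1.96 + 0.84)² / [(ln 0.7)² × (1/3)(2/3)] = 278. Post-period risk = 1 − 0.9^0.7 = 0.0711. Mean risk = (2 × 0.10 + 0.0711)/3 = 0.0904. Total = 278/0.0904 ≈ 3076, that is 1025 post and 2051 pre.
- Two proportions, 7% against 10%, no continuity correction: 1038 post and 2076 pre.

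Both are within 3% of 1021/2045. Both assume independent patients, which leaves no visible allowance for clinics.

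**2. Add clinic-by-period variation.** Let J be the number of equal-sized clinics and τ the between-clinic SD of the before-after log hazard ratio.

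- Naive variance = 1/e_post + 1/e_pre
- True variance = naive variance + τ²/J
- Type I error of the naive test = 2Φ(−1.96 × naive SE/true SE)

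The documents give neither J nor τ. Assumed ranges: J = 10 to 20, τ = 0.1 to 0.2. Events are taken under no intervention effect with 2000/4000 patients and the plan's 10% at 10 years: 200 and 400. For 5 years, half that risk is assumed: 100 and 200. Section 2.6 expects higher risk in the first years, so the 5-year event count may be low and the 5-year ratios correspondingly small.

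| Horizon | Naive variance | J, τ | τ²/J | True/naive SE | Type I error |
|---|---|---|---|---|---|
| 5 years | 1/100 + 1/200 = 0.0150 | 20, 0.1 | 0.0005 | √(0.0155/0.0150) = 1.02 | 5.4% |
| 5 years | 0.0150 | 10, 0.2 | 0.0040 | √(0.0190/0.0150) = 1.13 | 8.2% |
| 10 years | 1/200 + 1/400 = 0.0075 | 20, 0.1 | 0.0005 | √(0.0080/0.0075) = 1.03 | 5.8% |
| 10 years | 0.0075 | 10, 0.2 | 0.0040 | √(0.0115/0.0075) = 1.24 | 11.3% |

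As understatement of the true SE, the upper ends are 1 − 1/1.13 ≈ 11% at 5 years and 1 − 1/1.24 ≈ 19% at 10 years.

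**3. Check the mechanism.** Simulating a pooled two-period analysis under the null, with clinics differing only in a constant baseline risk, gives a naive type I error of 4.4% to 4.8%. There is no inflation, because each clinic contributes to both periods and its level cancels. Only differing changes matter.

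**4. Effect on power.** With 2000/4000, hazard ratio 0.7 and 10 years, events are about 140 and 400. With J = 10 and τ = 0.2 the variance is 1/140 + 1/400 + 0.0040 = 0.01364, SE 0.1168, and 0.3567/0.1168 = 3.05. Power is Φ(3.05 − 1.96) ≈ 86%, or about 79% with the t critical value on 9 degrees of freedom (2.26), against 95% without clustering.

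**The case against.** The strongest reply is that this argues from silence. The stroke model is not specified, the bracketed list concerns confounders rather than the variance estimator, and a condensed article may leave clustered standard errors to an analysis plan that is not shown. A reader might infer that the final model is known to ignore clinic and that its interval is certainly too narrow; the document does not support that. What it does support is a mismatch between things the article itself fixes: a cluster-based design beside a covariate list, strata and a sample size that all leave clinic out. Table 2 labels the analysis as matched, but no matching is described, so the label does not close the gap.

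Three further points limit the concern.

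- A reader might infer that differing baseline stroke rates between clinics narrow the interval, or that clinics switch on staggered dates. The first is wrong here, as step 3 of the working shows. The second is only suggested by the reference to each center's implementation phase; no dates are given, and the argument does not need them.
- Local discretion over work-up and prescribing creates variation in the intervention's effect. If the intervention does nothing in any clinic, that discretion has nothing to act on. The type I figures therefore need clinic-specific changes in stroke rate that would occur anyway. Such trends are plausible, but the protocol does not document them. Shared guidelines and regular site education also limit divergence.
- The assumed τ is unsupported. At 0.2, 95% of clinics would have true before-after hazard ratios between exp(−0.392) = 0.68 and exp(0.392) = 1.48, which is wide. At the low end the effect is slight.

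The sample-size consequence is also modest. The expected inclusion is nearly double the stated requirement, and power stays at about 79% to 86% even in the least favorable case assumed.

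**Conclusion.** The concern holds as a mismatch between design and stated analysis. Clinics are the unit of change, yet the lists in 2.5 and the sample size in 2.6 take no account of them. Following 2.5 as written would understate the uncertainty of the stroke comparison if clinics differ in their before-after change, and not if they differ only in level.

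The size cannot be derived from the document. Under the stated assumptions on clinic number and between-clinic SD, it runs from negligible (true SE 2% above the naive SE at 5 years) to material (24% above it at 10 years, type I error 11.3%). The type I figures further assume local changes in stroke rate unrelated to the intervention. The planned study is not shown to be underpowered at its expected size. The change is worth making because the correction is cheap and the primary cohort result depends on it.

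**What to change.** In 2.5, stratify the stroke and mortality models by clinic, so that each clinic's post-period patients are compared with its own earlier patients. Base the confidence interval on clinic-level robust variance with a small-sample correction, or include a random clinic-by-period effect. Both parts are needed: stratification makes each clinic its own control and guards against a shift in clinic mix between periods, but it does not by itself correct the standard error. State the choice before outcome data are extracted.

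In 2.6, say that 1021/2045 assumes independent patients and is a lower bound, and give the planned number of clinics.

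The cost is a few sentences. Clinic must already be identified to apply the eligibility rule in 2.3, so no new data are needed. The downside is a somewhat wider interval, more so if few clinics take part.
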